#### Allocation concealment

The site Data Managers will be entrusted with keeping the allocation list secure (through password protected files). The matching of the study numbers of the recruited participants with their randomization numbers and the concealment of randomization from interviewers will also be managed by the central Data Manager to ensure that no one has access to the allocation list.

#### Implementation

For logistic reasons, the site Data Managers will be responsible for assigning the unique trial ID for each randomized participant in the trial; if the participant is assigned to the CCBC arm, the Data Manager will notify the site intervention coordinator and pass on the required contact information. For participants in both arms, the Data Manager will also ensure that treating Psychiatrists are provided with the specially designed clinical booklet to record treatment details for the next 12 months.

For statistical reasons (see 'sample size estimation' below) there will be unequal allocation, with a larger number in the intervention arm. The rationale for the unequal randomization is the additional source of variability in the intervention arm - the effect of individual community health workers which is built into the analysis and allowed for in the sample size as recommended in the recent CONSORT guidelines for non pharmacological trial design and reporting[15]. It is difficult to precisely estimate the magnitude of this extra variability (the intra-class correlation), but the value chosen for the intervention arm of 0.1 is conservative: a recent review of a large number of primary care variables found the inter-quartile range to be 0 to 0.032[16]. For practical reasons, the ratio of numbers in the two arms was fixed at a whole number; for the study this has been chosen to be 2:1. The method of allocation will be through the use of permuted blocks, with random block sizes chosen from 3, 6 and 9 using the '*ralloc*' routine in Stata.

##### Outcome assessments

###### 1. Quantitative assessments

For the primary outcome assessments, we will record the *symptoms of schizophrenia *at baseline and at 12 months, with the Positive and Negative Syndrome Scale (PANSS) [17].

For measuring the *change in disability*, we will use the Indian Disability Evaluation and Assessment Scale (IDEAS)[18] at baseline, 6 and 12 months to generate information on the time course of the effect of the intervention.

For the secondary outcome assessment for persons with schizophrenia, we will measure:

• *Adherence with antipsychotic medication*: For each participant, we will assess adherence at baseline (if on treatment) and at 6 and 12 months using a 5 point ordinal scale developed for the study.

• For measuring *various dimensions of the experience of stigma and discrimination*, we will use the Discrimination and Stigma Scale (DISC)[19] at baseline and at 12 months.

• An item on *willingness to disclose mental illness *[20] will be used for participants at baseline and at 12 months to assess their readiness to disclose their illness.

• The Alienation subscale of the Internalized Stigma of Mental Illness (ISMI) scale[21] will be used to measure the *subjective experience of internalized stigma of participants *at baseline and at 12 months.

• Finally, to estimate the *Quality Adjusted Life Years (QALY)*, we will use the widely used Euroqol (EQ-5D) [22] at baseline and at 12 months.

**The secondary outcome measure for the **primary care givers are:

• The *family burden of caring *will be measured at baseline and at 12 months by using the Burden Assessment Schedule (BAS) which has been developed and used widely in India[23].

• The *knowledge and attitudes of family members about schizophrenia *will be assessed at baseline and at 12 months by using the Knowledge about Schizophrenia Interview (KASI) [24]

• A section of the 'Family Interview Schedule' (FIS) developed for the International Study of Schizophrenia (ISOS)[25] and previously used in a study in India[26] will be employed to assess *the experiences of stigma and discrimination experienced by the primary caregivers*.

• The item on *willingness to disclose mental illness *[20]will be used for caregivers after suitable modification.

• The *caregiver summary assessment of the participant's degree of adherence *will be rated by using the same 5 point ordinal scale used for participants. To improve the validity of adherence ratings, we will complete a systematic assessment of medication use for the last 2 months (to minimize recall bias over the 6 month period); this 2 month adherence will be extrapolated for the last 6 months.

For the economic aspects of the study, we will ask caregivers to complete the Cost of Illness Schedule (CIS) that has been developed and used in India in community studies before[27] at baseline, 6 and 12 months. In addition, we will record the type, dosage and duration of medications prescribed by treating Psychiatrists during each of the contacts with participants as well as the number of inpatient days for each participant - this data will be available from the Psychiatrists' structured records. Service costs will be calculated by attaching locally calculated unit costs to these data. In addition, we will use the Euroqol EQ-5D with participants for assessing Quality of Life Years at baseline and at 12 months.

The adherence measures and the CIS will be repeated at 6 months, as will the IDEAS. For the CIS and adherence measures, the rationale is to minimize recall bias. The IDEAS will be used at 6 months to have an interim measure for one of the primary outcomes that is brief and easy to complete.

Table 2 describes the data collection details of the study.

**Table 2 T2:** Summary table of data collection in COPSI.

TYPE OF DATA					
**1. Quantitative**: (using a combination of programmed palmtops and paper and pencil methods)			**Measured at**:		

**Primary Outcome**	**Interviewee**	**Outcome assessment scale description**	**0 month**	**6 months**	**12 months**

Symptoms	Person with schizophrenia	*Positive and Negative Syndrome Scale (PANSS)*. The PANSS has 30 items to record current psychopathology on 3 domains- positive symptoms, negative symptoms and general psychopathology; each item rated on 1-7 scale thus having a total score range of 30-210.	**X**		**X**

Disability	Primary caregivers	*Indian Disability Evaluation and Assessment Scale (IDEAS)*. For the IDEAS evaluation, the participant is assessed on 4 domains- Self Care, Interpersonal Activities, Communication and Understanding and Work. The scale generates a global score of 0-20 with increasing scores indicating more severe disabilities	**X**	**X**	**X**

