### Objectives

The objectives of the trial are: firstly, to test the hypotheses that usual, Facility-Based Care (FBC), when combined with a Collaborative Community-Based Care intervention (CCBC), will be superior to Facility-Based Care alone in improving a range of outcomes in people with schizophrenia and their caregivers and, secondly, to determine if the CCBC intervention is cost effective in India.

The primary objectives of the trial are to determine whether the FBC+CCBC intervention will be superior to FBC alone in:

i) reducing symptoms of schizophrenia at 12 months, and

ii) reducing disability related to schizophrenia over 12 months.

In *persons with schizophrenia*, the secondary objectives are to determine whether, FBC+CCBC will be more effective than FBC alone, in:

• improving adherence to antipsychotic treatment

• reducing experiences of stigma and discrimination

For *caregivers of people with schizophrenia*, the secondary objectives are to determine

whether, FBC+ CCBC will be superior to FBC alone, in:

• improving their knowledge and attitudes about the illness

• reducing their burden of caring

• reducing experiences of stigma and discrimination.

The health economic objective is to compare the costs and assess the cost-effectiveness and cost-utility of the FBC+ CCBC intervention compared to FBC alone.

The COPSI trial is a collaborative effort between multiple institutions and individual Psychiatrists at the Indian sites. The lead institution is the Institute of Psychiatry (IoP), Kings' College, London, while the partner organizations are the London School of Hygiene and Tropical Medicine (LSHTM), Sangath in Goa, the Schizophrenia Research Foundation (SCARF) in Chennai, the National Institute of Mental Health and Neuroscience (NIMHANS) in Bangalore and Parivartan and Nirmittee in Satara. In Goa and in Satara, the individual collaborators are Psychiatrists working in the private sector.

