##### Analysis plan for economic data

Service costs will be calculated by combining the service use data with appropriate local unit costs. Cost comparisons will be made using bootstrapping methods to account for skewed data. Cost-effectiveness will be assessed by combining costs with outcomes in the form of incremental cost-effectiveness ratios which will show the extra cost incurred (if any) to produce a unit improvement in the main outcomes (symptoms and disability) as well as QALYs (measured using the EQ-5D combined with appropriate utility weights). Uncertainty around cost-effectiveness estimates will be explored using cost-effectiveness planes and interpretation will be aided using cost-effectiveness acceptability curves.

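### EQ-5D is measured only at baseline and 12 months, so the QALY result rests on an untestable path between two points although participants are already interviewed at 6 months

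*Protocol article*

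**What the plan says.** The Protocol article's Objectives section sets the health economic aim: to "compare the costs and assess the cost-effectiveness and cost-utility of the FBC+ CCBC intervention compared to FBC alone". The section Analysis plan for economic data puts costs into incremental ratios against symptoms and disability, "as well as QALYs (measured using the EQ-5D combined with appropriate utility weights").

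The EQ-5D schedule is given three times, consistently. Under Quantitative assessments, for estimating QALYs, "we will use the widely used Euroqol (EQ-5D) [22] at baseline and at 12 months". The economic paragraph of the same section repeats it: "we will use the Euroqol EQ-5D with participants for assessing Quality of Life Years at baseline and at 12 months". Table 2 marks the instrument at 0 and 12 months only.

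Other measures have a middle time point: "The adherence measures and the CIS will be repeated at 6 months, as will the IDEAS". The reason given for the Cost of Illness Schedule (CIS) and adherence is to limit recall bias. The IDEAS is taken "at baseline, 6 and 12 months to generate information on the time course of the effect of the intervention", and also because it offers a short, simple mid-trial reading of a primary outcome. No reason is given for leaving the EQ-5D out at 6 months.

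Table 2 lists the participant's own adherence rating at 6 months, and the section on outcome evaluation and masking refers to interviews at 6 and 12 months. An interview with the right respondent therefore already exists.

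**The concern.** A QALY is the area under a utility curve over time, so it depends on when benefit arrives as well as on how much is present at the end. Two measurements fix the end points and say nothing about the shape between them. Planned CCBC contacts thin out over the year and the content of the three phases changes, so there is no particular reason to expect utility to move at a constant rate.

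What is at stake is the denominator of the cost per QALY. It would rest on an assumption about shape that the trial's utility data can neither support nor contradict. Utilities not collected at 6 months cannot be recovered by any later analysis plan.

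**Working it through.** **Inputs from the Protocol article.** EQ-5D at 0 and 12 months; follow-up of 12 months; planned contacts of 6 to 8 in months 1 to 3, 6 to 8 in months 4 to 7, and 6 in months 8 to 12; a stated maximum of 22 contacts.

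**Reproducing the stated figure.** 8 + 8 + 6 = 22, which matches. The lower counts give 6 + 6 + 6 = 18.

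**How early the contacts fall.** Monthly rates are 6/3 to 8/3 = 2.0 to 2.7, then 6/4 to 8/4 = 1.5 to 2.0, then 6/5 = 1.2. With even spacing within phases, contacts by month 6 are 6 + 6 × 3/4 = 10.5 of 18 (58%) to 8 + 8 × 3/4 = 14 of 22 (64%). The loading is early but mild.

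**Assumptions.** The between-arm utility difference is 0 at baseline and D at 12 months. The documents do not give D, so results are multiples of it. Every path below is assumed.

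**Formulas.**
- Two points: gain = (0 + D)/2 × 1 year = 0.50D.
- Three points, with difference m at month 6: gain = 0.5 × (0 + m)/2 + 0.5 × (m + D)/2 = 0.5m + 0.25D.
- For a fixed extra cost, reported over true cost per QALY = true gain / 0.50D.

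The two formulas agree only if m = D/2, which is the quantity a 6-month EQ-5D would measure.

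**Area if benefit tracks cumulative contacts.**
- Upper counts, with fractions 8/22, 16/22 and 1 at months 3, 7 and 12: (3/12)(0.364/2) + (4/12)(0.364 + 0.727)/2 + (5/12)(0.727 + 1)/2 = 0.045 + 0.182 + 0.360 = 0.587.
- Lower counts, with fractions 6/18, 12/18 and 1: 0.042 + 0.167 + 0.347 = 0.556.

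| Assumed path of the difference | True gain | Two-point gain / true | Cost per QALY, reported / true | Three-point gain |
|---|---|---|---|---|
| Straight line | 0.50D | 1.00 | 1.00 | 0.50D |
| Tracks contacts, lower counts | 0.556D | 0.90 | 1.11 | 0.542D |
| Tracks contacts, upper counts | 0.587D | 0.85 | 1.17 | 0.568D |
| Linear to D by month 6, then held | 0.75D | 0.67 | 1.50 | 0.75D |
| Linear to D by month 3, then held | 0.875D | 0.57 | 1.75 | 0.75D |
| None to month 6, then linear to D | 0.25D | 2.00 | 0.50 | 0.25D |

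These paths are not bounds. A difference that peaks at 1.5D at month 6 and falls back to D gives 0.5 × 1.5D + 0.25D = 1.0D, and the reported cost per QALY would be twice the true one.

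**What a third point buys.** The three-point value is exact where the only bend is at month 6. It is about 3% short if benefit tracks contacts (against 10 to 15% short with two points), and 14% short if benefit is complete by month 3 (against 43%).

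**The case against.** A reader might infer that CCBC is front-loaded, that a straight line is therefore the least likely shape, and that the cost-utility result will be badly off to the disadvantage of CCBC. The documents do not support this. Only 58 to 64% of contacts fall in the first half of the year, and a benefit that follows them is close to linear, with the QALY gain 10 to 15% short. Content also leans the other way. Engagement, needs assessment, adherence work and psycho-education come first. Daily-living and social skills work is introduced in months 4 to 7, and social and economic roles are addressed in months 8 to 12. Those later parts bear on the EQ-5D domains of self-care and usual activities, so a late gain is as credible as an early one. The larger errors in the table come from assumed paths that point in opposite directions.

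The straight line is itself an inference, since the article states no rule for joining the two utilities. Such a rule, and any sensitivity analysis on it, may properly sit in an economic analysis plan that is not shown; its absence here is not a fault.

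The contrast with costs is also limited. The CIS is repeated to reduce recall bias, so collecting costs at 6 months without utilities is not a contradiction. The 6-month IDEAS gives some information on timing, although it is a disability scale answered by the caregiver and cannot replace a utility.

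All of this stands, and it narrows the point. It leaves untouched that the measurement schedule is fixed in the protocol, that the 6-month participant interview already exists, and that two points cannot test any path.

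**Conclusion.** The point holds as an inexpensive improvement to the design; it is not an error or contradiction in the plan. The cost per QALY will depend on an untestable path between two utility values. Its error could be around 11 to 17% upward if benefit follows contacts, 50% upward if benefit is complete by month 6 and held, or a halving if benefit comes only after month 6. The direction cannot be known beforehand.

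These sizes assume no baseline difference in utility, a fixed extra cost, even spacing of contacts within phases, and straight-line joining of the two EQ-5D values. The consequence is confined to the cost-utility result. PANSS, IDEAS and the cost per unit of symptom or disability improvement do not depend on the EQ-5D schedule.

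**What to change.** Add the EQ-5D to the existing 6-month participant interview, mark that time point in Table 2, and compute QALYs from the three measurements. The cost is five three-level items and one visual scale, a few minutes of participant time and a small form change; no new visit is needed.

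If follow-up is already past that stage, report the QALY difference and cost per QALY under an early-gain and a late-gain path alongside the straight line, and use the 6-month IDEAS to judge which is more plausible. This costs only analysis time. It shows the uncertainty but does not remove it.

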**Secondary outcomes**					

Stigma and discrimination	Person with schizophrenia	*Discrimination and Stigma Scale (DISC)*. The version to be used is based on DISC-12, but was adapted for the study. The revised version has 30 items in total, all rated on a 4 point Likert scale ranging from 'not at all' to 'a lot'.	**X**		**X**
		There are 20 items in the Negative Discrimination Subscale plus 1 new negative discrimination item generated for the trial, 4 items on anticipated discrimination, 1 item relating to efforts of overcoming stigma and discrimination and 4 items for recording experiences of positive discrimination.			
		
Internalized stigma		*The Internalized Stigma of Mental Illness (ISMI) scale *is designed to measure the subjective experience of internalized stigma and consists of 5 subscales. For the study, the 'Alienation' subscale was chosen. It consists of 6 items which are scored on a 4-point Likert scale ranging from 'strongly disagree' to 'strongly agree'.	**X**		**X**
		
Willingness to disclose illness		An item on willingness to disclose mental illness rated on a 5-point Likert scale ranging from 'very uncomfortable' to 'very comfortable'.	**X**		**X**
		
Quality of life		Euroqol EQ-5D that has a descriptive assessment of 5 domains: mobility, self-care, usual activities, pain/discomfort, anxiety/depression. Each domain is coded as level 1, 2 or 3 and combined into a 5 digit code together with a summary visual analogue scale assessment of quality of life score 0-100.	**X**		**X**
		
Subjective rating of adherence with antipsychotic medication		Adherence rating tool with 5 ordinal ratings to describe a range of adherence (from non adherent- fully adherent)	**X**	**X**	**X**

Knowledge of and attitudes towards illness	Primary caregiver(s)	*Knowledge about Schizophrenia Interview (KASI)*. There are 6 domains of understanding that are assessed; the maximum score for each domain being 4.	**X**		**X**
		
The family burden of caring		*The Burden Assessment Schedule (BAS)*. The BAS is scored on 40 items with a maximum score of 120; the minimum score can be less than 40 as some questions can be rated as 'not applicable'.	**X**		**X**
		
Costs of illness		Cost of Illness Schedule (CIS)	**X**	**X**	**X**
		
Adherence with antipsychotic medication		Adherence rating tool with 5 ordinal ratings ranging from non- adherent to fully adherent supplemented by audit of actual medicine use over last 2 months that is extrapolated to the previous 6 month period	**X**	**X**	**X**
		
Experiences of stigma and discrimination		14 items from the Stigma section of the *Family Interview Schedule (FIS) *will be used to assess the experiences of stigma the primary caregivers. These cover several aspects of internalized stigma as well including perceived need to conceal the illness and anticipated discrimination. The items are scored on a 4-point Likert scale (0 - 3) ranging from 'not at all' to 'a lot'.	**X**		**X**
		
Willingness to disclose		Item on willingness to disclose mental illness rated on a 5-point Likert scale ranging from 'very uncomfortable' to 'very comfortable'.	**X**		**X**

**2. Clinical outcomes of interest**:	**Information source**	**How recorded?**	**Frequency of measurement**		

Treating Psychiatrist's assessment of overall clinical change	Clinical records maintained by treating Psychiatrist	Clinical Global Impression-Schizophrenia 'overall change' scale section	Every 3 months		
					
Treating Psychiatrist's assessment of adherence		5 point nominal measure, similar to that used by participants and caregivers	Every 3 months		
					
Inpatient stay details		Recorded for each such episode by treating Psychiatrist	Collated at endpoint		
					
Relapse of illness		Relapse is defined as clinically significant exacerbations of symptoms after at least 2 months of well- being; clinical significance involves meeting at least 2 of the following 3 criteria: marked increase in positive symptoms, hospitalization for acute care and significant increase in dosage of antipsychotic medications	Collated at endpoint		
					
Serious antipsychotic medication side effects	As above; also during by 6 and 12 month outcome assessments.		Collated at endpoint		
			
**3. Process indicators**					
			
A. For participants in both arms of study	Clinical records maintained by treating Psychiatrist	Number of contacts with treating Psychiatrists Type (face to face or telephone) contacts Treatment details- use of psychotropic medications and Electro Convulsive Treatments			
B. For participants in the CCBC arm	Individual care plan records maintained by the Community Health Workers' (CHW's)	The delivery of the components of the intervention as per protocol over the 3 phases of the intervention	Collated at endpoint		
		Per protocol supervision for CHW's	Every 3 months		
		Total number of contact by the CHW's during the 12 month period of the intervention	Every 3 months		

Finally, we will record other presence of co-morbid mental and physical disorders and relevant socio- demographic information about the participant, the primary caregiver and the family during the baseline assessment.

####### Outcome evaluation/masking

The outcome evaluation of symptoms using the PANSS will be carried out by mental health professionals who will be trained, certified and supervised by experts. All other outcome measurements will be conducted by trained graduate researchers. The selected researchers will be trained in a structured manner across the sites to ensure adequate inter-rater reliability for all scale items across the sites. To maintain blinding of these assessments, all outcome measures will be administered by researchers who are independent of the intervention and blind to the allocation of treatment. Since neither the participant nor the family caregivers will be blind to their allocation status at the time of the 6 and 12 month interviews, we intend to minimize the chances of unmasking during the outcome assessments by instituting the following measures:

• The intervention and research teams at the sites will not have any interactions during the trial with separate physical location and administrative management.

• The researchers are told that they are evaluating two interventions and that there is genuine equipoise about which one is better

• Orient the families prior to each assessment that they should not disclose whether or not they are receiving home visits from the CHW and

• Complete the primary outcome measures (PANSS and the IDEAS) first.

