### Description of the Interventions

#### The collaborative community based care (CCBC) intervention

The CCBC intervention is underpinned by three key principles:

• firstly, the intervention is planned and implemented for each participant in close collaboration between the person with schizophrenia, the primary care giver(s) and the treatment team members (comprising the lay CHW, a supervising Psychiatric Social Worker and the treating Psychiatrist);

• secondly that the intervention is provided in a flexible manner that reflects the unique needs of the person with schizophrenia and their caregivers and;

• thirdly, that the intervention will promote respect, autonomy and dignity for the person with schizophrenia and caregivers.

The inclusion of the specific treatment components within the treatment package have been guided by:

• evidence that the treatment is locally feasible, acceptable and potentially of low cost;

• evidence for the effectiveness of the treatment in low and middle income settings and;

• evidence that it can be delivered by lay health workers

The CCBC intervention will be coordinated and delivered by lay CHWs who have completed at least 10 years of schooling and have been systematically trained at each site over 6 weeks. The training is based on the intervention manual that follows a modular structure covering various aspects of the illness, specific components of the intervention and the operational requirements of the trial related documentation and supervision http://www.sangath.com/details.php?nav_id=60. The CHWs will be closely supervised at each site by Psychiatric Social Workers working as designated Intervention Coordinators. They will coordinate the overall delivery of the intervention and assure the quality and fidelity of the intervention at the site. The treating Psychiatrists will provide clinical leadership for the community care teams and ongoing supervision to maintain safety and quality standards. Overall, the continued supervision of the CHWs through joint onsite visits, weekly group meetings and in scheduled meetings with the Psychiatrist is an essential component of the CCBC intervention.

The treatments included in the intervention package are:

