#### Facility based Care (FBC)

'Facility Based Care' is the care usually provided by mental health practitioners for persons with schizophrenia and their families. In two of the sites i.e. Goa and Satara, Psychiatrists in the private sector are the primary care providers with trained assistants recording essential socio demographic details in some of these clinics. In rural Tamil Nadu, a team of three persons are involved in the clinics. A trained assistant records essential socio demographic details of all persons who come to the clinic. A brief clinical history is then elicited by the Psychiatric Social worker (PSW) who then presents the findings to the clinic Psychiatrist for detailed assessment and treatment planning. In Goa and in Satara, the Psychiatrists are the first point of contact and, for the most part, conduct all necessary procedures themselves. Across all settings, consultations last from 15-45 minutes; persons with schizophrenia presenting for the first time are reviewed once or twice a month while those who are clinically stable are reviewed more flexibly- once a month- 3 months. Almost all persons with schizophrenia in these facilities are prescribed psychotropic medications with the newer antipsychotic medications being preferred (as in India, these newer drugs are cost comparable with the older antipsychotic drugs) while the use of antidepressants, anticholinergic, sedatives and modified Electroconvulsive treatment (ECT) is based on individual clinical needs. All psychiatrists also provide specific information about the illness, encourage adherence and discuss other specific concerns that the person with schizophrenia or their family members have; all of these are provided on an 'as needed' basis. The salient difference between the two arms is that in the CCBC arm, a complex psychosocial intervention, tailored towards individual needs, will be delivered in an accessible (home based) and structured manner by a dedicated CHW. There will be no guidelines or protocols made available to Psychiatrists for the medical treatment of participants as this is more representative of usual care in India. FBC will continue to be available to participants in both study arms and treating Psychiatrists will be unblinded while providing care for participants.

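### The masking statement covers all outcome measures, but CGI-SCH change, psychiatrist-rated adherence and relapse come from unblinded psychiatrists who lead the CCBC teams

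*Protocol article*

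**What the plan says.** Under Outcome evaluation/masking, the protocol gives the PANSS to trained mental health professionals and then states: "All other outcome measurements will be conducted by trained graduate researchers". It goes on to say that "all outcome measures will be administered by researchers who are independent of the intervention and blind to the allocation of treatment". Neither sentence carries an exception.

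Table 2 has three numbered sections. The first holds the primary and secondary outcomes. The second is headed "Clinical outcomes of interest". Its first row is "Treating Psychiatrist's assessment of overall clinical change", scored on the overall-change section of the CGI-SCH, and its second is "Treating Psychiatrist's assessment of adherence". Both are made every 3 months, and the information source is "Clinical records maintained by treating Psychiatrist". Inpatient stay, relapse and serious medication side effects follow, all compiled at the end of follow-up.

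On the people who supply this information, the Facility based Care section says that "treating Psychiatrists will be unblinded while providing care for participants". The CCBC section says: "The treating Psychiatrists will provide clinical leadership for the community care teams". It also counts the treating psychiatrist as a member of the treatment team and gives that person a part in supervising the community health workers (CHWs).

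**The concern.** The protocol claims two properties for every outcome measure: the assessor is blind, and the assessor is independent of the intervention. For the psychiatrist-recorded measures, its own text denies both.

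This matters because CGI overall change is a global clinical impression. It is also the only scheduled rating of overall clinical change between the two PANSS assessments at baseline and 12 months; the 6-month IDEAS measures disability. Relapse likewise depends partly on the psychiatrist's judgement and prescribing. If either measure differed between arms and was reported under a general statement of blinded assessment, a reader could take it as masked support for the PANSS result.

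The direction of any bias is not certain. A rater who leads the intervention may expect CCBC to do better. On the other hand, Ethical considerations has CHWs report critical incidents in the CCBC arm only, and closer observation of that arm could raise its event counts.

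**Working it through.** No figure in the protocol depends on this point, so nothing is recalculated. The check compares each item in the Table 2 block with the two claimed properties.

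| Item | Source | Timing | Researcher source as well? | Does the masking claim hold? |
|---|---|---|---|---|
| CGI-SCH overall change | Treating psychiatrist, named in the row | Every 3 months | No | No |
| Psychiatrist-rated adherence | Treating psychiatrist, named in the row | Every 3 months | No (participant and caregiver ratings are separate measures) | No |
| Inpatient stay | Treating psychiatrist, named in the row | End of follow-up | Partly: researchers record hospitalisation at 6 and 12 months (Ethical considerations) | Not for the psychiatrist's record, but more objective |
| Relapse | Psychiatrist's records, read from the source cell that carries down | End of follow-up | None stated | No |
| Serious side effects | Psychiatrist's records and the 6- and 12-month assessments | End of follow-up | Yes | In part |

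1. **Blindness.** The Facility based Care section says that the psychiatrists are unblinded. Any item that rests on their rating alone is an unblinded item.

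2. **Independence.** The CCBC section makes them clinical leaders of the teams that deliver the intervention. They are not independent of it.

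3. **Relapse.** Table 2 requires at least 2 of 3 criteria: a marked worsening of positive symptoms, admission for acute care, and a significant rise in antipsychotic dose. The first is a judgement and the third follows the treating psychiatrist's own prescribing. Only one criterion, admission, lies outside these two. Since two must be met, every relapse includes at least one that rests on that psychiatrist's judgement or decision.

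4. **What stays masked.** PANSS goes to trained mental health professionals. IDEAS and the listed secondary outcomes go to the graduate researchers. The masking statement covers both groups, and nothing in the protocol contradicts it for these measures.

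5. **What the analysis uses.** The Objectives, the outcome list under Quantitative assessments, and Data management and analysis do not name CGI change, psychiatrist-rated adherence or relapse. The adherence proportions to be reported by arm come from the caregiver ratings. Inpatient days enter the cost calculation.

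Three of the five items therefore contradict the masking statement outright. The other two do so only in part or with less consequence.

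**The case against.** The best defence is context. The masking sentence opens by referring back to the assessments just described, speaks of measures being administered, and leads into the 6- and 12-month interviews. Table 2 also separates interview-based outcomes, which have an interviewee column, from record-based ones, which have an information-source column. The authors may well have meant only the first group. That reading is plausible, but it is not written. It also does not rescue the preceding sentence, which gives all remaining outcome measurements to graduate researchers without a limit, while the table calls the psychiatrist-recorded items outcomes.

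A second defence is that nothing is concealed: the table rows name the treating psychiatrist, and the Facility based Care section says that psychiatrists are unblinded. This is correct, and there is no ground to suggest concealment. But that section describes the psychiatrists as care providers, not as outcome raters, and the masking section says the opposite of what the table shows.

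The third defence stands in full: these measures sit below the primary and secondary outcomes, and no efficacy analysis in the protocol relies on them.

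Several stronger readings are tempting but not supported:

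- *The whole block is outside the masking.* Hospitalisation and serious side effects also have a researcher source.
- *Relapse is a repeated unblinded rating.* It is compiled once, at the end; only CGI change and psychiatrist-rated adherence are repeated.
- *The trial's adherence result is unblinded.* The reported proportions come from the caregiver ratings, which researchers collect.
- *The number of ratings shows the size of the problem.* Four quarterly ratings in 282 participants give at most 282 × 4 = 1,128 forms per instrument. That counts forms, not bias.

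**Conclusion.** The contradiction is real. The protocol states a masking property that its design does not have for CGI-SCH overall change, psychiatrist-rated adherence and relapse. For relapse this assumes that the blank source cell carries down from the rows above, which is the natural reading because the side-effects row below refers back to the same source.

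The consequence is for interpretation. A difference between arms in these three measures is open to rater expectation and to unequal information, in a direction and of a size that the protocol does not let one estimate. A reader might infer that the primary comparison is compromised. It is not: the PANSS and IDEAS assessments and the listed secondary outcomes are untouched by this point. The correction should be made because it is cheap and because an unqualified blinding statement tends to carry over into the trial report.

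**What to change.** Make two changes of wording.

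1. In Outcome evaluation/masking, limit both sentences to the primary and secondary outcomes administered by the researchers and PANSS assessors.
2. In Table 2, label the psychiatrist-recorded outcomes as unblinded and descriptive. State that differences between arms in CGI change, psychiatrist-rated adherence and relapse will not be presented as masked evidence of efficacy. Note there that hospitalisation and serious side effects are also captured by researchers at 6 and 12 months.

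No visit, staff or data collection is added. The cost is that the 3-monthly CGI and adherence series, and relapse, can no longer be cited as independent support for the PANSS result.

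An additional blinded CGI severity rating at baseline and 12 months is not needed. It would largely duplicate the PANSS at the same two time points and would supply nothing between them. Recording the treating clinician's view as a third tier is an ordinary choice in a trial of routine care and can stay.
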